### Intervention

Our study protocol basically follows that of the SNT study.^23^ A MagVenture MagPro R30 (MagVenture A/S) system and a double‐sided Cool‐B70 A/P coil will be used to deliver sessions of iTBS; 60 cycles of 10 bursts of three pulses at 50 Hz were delivered in 2‐s trains (5 Hz) with an 8‐s intertrain interval. Ten sessions will be applied per day (18,000 pulses/day) for 5 consecutive days (90,000 pulses in total). We will use BeamF3 for coil localization/targeting method.^33^ Recently, Sheline and colleagues reported that aiTBS (L‐DLPFC) similar to SNT protocol improved the depressive symptoms in patients with TR‐BDep.^34^ The resting motor threshold (RMT) of Sheline's study was 90%.^34^ Therefore, we decided that stimulation will be delivered at 90% of the RMT in our study. First, beginning at 40% of maximal stimulator output, the approximate RMT will be determined by moving the coil and adjusting the power level until exactly three right thumb twitches during five consecutive pulses are produced. In this step, the stimulus intensity will be gradually increased in steps of 5% of the maximal stimulator output. Second, the almost RMT will be determined by decreasing the stimulus intensity in 1% steps, as the minimum intensity (as a percentage of the maximal stimulator output) that will produce exactly two right thumb twitches during five consecutive pulses. Finally, the RMT will be determined as the almost RMT plus 1% stimulus intensity. We also referred to the Japanese rTMS text^35^ and a previous systematic review^36^ for these methods. A specially designed rTMS coil with both an active and a sham inductor head including an identical external appearance will be employed to ensure blindness during treatment. Sham treatment will include a simultaneous electric pulse to mimic aiTBS sensation. Participants will be seated in a designated waiting area that will not be shared by study staff or other patients in between treatments. This will be conducted to limit interaction time with study staff and to avoid a group effect. All iTBS sessions will be performed in the Department of Psychiatry at Fujita Health University Hospital.

Because we want to develop an aiTBS protocol that is more convenient in clinical practice than SNT,^23^ the SNT protocol was modified in the following manner: (1) For coil localization/targeting method, SNT uses MRI. We will use BeamF3^33^ instead of MRI because our meta‐regression analysis demonstrated no differences in the effect size of iTBS (L‐DLPFC) for the improvement of depressive symptoms between studies using MRI and those that did not.^22^ Sheline's study also used MRI for determining the stimulation target.^34^ (2) For intersession interval, the intersession interval of SNT and Sheline's study was 50 min. The intersession interval of our study will be 30–50 min because our meta‐regression analysis revealed that length of intersession interval was unrelated to the magnitude of effect size of iTBS (L‐DLPFC) for the improvement of depressive symptoms.^22^ We refer to this aiTBS protocol as Fujita Neuromodulation Therapy for Bipolar Depression (FNT‐BD).

### Randomization and blinding

Eligible participants will be randomly assigned (1:1) to either aiTBS or a sham treatment using a computer‐generated list of random numbers. Randomization will be stratified by sex (men vs. women) and age (<46 or ≥46 years). The age threshold was established at 46 years because the median age of outpatients at our hospital who satisfied the TR‐BDep criteria as defined in this study was 46 years. The allocation sequences will be added to the Research Electronic Data Capture (REDCap) electronic database.^37^, ^38^ An independent researcher from the Center for Clinical Trial and Research Support, Fujita Health University School of Medicine will conduct the randomization and allocation. The sequence will be unknown to all participants, caregivers, clinical assessors, treatment providers, and other study personnel.

All participants, caregivers, clinical assessors, treatment providers, and other study personnel will be unaware of their treatment assignments. Clinical assessors and treatment providers will be separate entities. Participants will be instructed not to discuss stimulation sensations with the study personnel. Each iTBS session will use the same stimulation coil, with no indication of active or sham orientation. Hence, all participants, clinical assessors, treatment providers, and other study personnel should be unable to infer that sham treatment will be used, that is, they should be unaware of the stimulation condition.

### Sample size calculation

According to the SNT study data (response rate at any week of follow‐up in the aiTBS group and sham group was 85.7% and 26.7%, respectively),^24^ allocating 11 participants to each arm will ensure ≥80% power to detect the superiority of the aiTBS compared to the sham group regarding the primary outcome. A chi‐square test and a two‐tailed test were used to determine the sample size with a statistical significance of 0.05. Because approximately 7% of randomized participants dropped out of the SNT study,^24^ we factored this information into our sample size calculation.

### Statistical analysis

Descriptive statistics will be computed for all variables of interest. Continuous measures, like age, will be summarized using means and standard deviations, while categorical measures will be summarized with counts and percentages. The data will be analyzed on a full analysis set, with endpoint analysis using the last‐observation‐carried forward method. The full analysis set will include all patients who agree to provide a baseline and at least one postbaseline data measurement. Response and remission rates will be evaluated using a *χ*
^2^ test. In Week 6, the MADRS score will be calculated using generalized linear mixed models. All statistical tests will be two‐sided, with significance defined as *p* < 0.05.

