### Primary and secondary outcome measures

The response rate at any given week of follow‐up is the primary efficacy outcome. The response will be defined as a reduction of ≥50% in the Montgomery Åsberg Depression Rating Scale (MADRS)^32^ score. Secondary efficacy outcomes include response rate at 5–7 days, Week 2, 4, and 6; changes in the MADRS score at 5–7 days, Week 2, 4, and 6; remission rate (10 ≥ MADRS score) at 5–7 days, Week 2, 4, and 6; Clinical Global Impression‐Improvement^28^ score at 5–7 days, Week 2, 4, and 6; CGI‐S for mania^28^ score at 5–7 days, Week 2, 4, and 6; and CGI‐S for depression^28^ score at 5–7 days, Week 2, 4, and 6. The definitions of “response” and “remission” in our study are the same as that of the SNT study.^23^, ^24^ Table 2 illustrates the schedule of these psychometric assessments. Other outcomes include the discontinuation rate and the incidence of individual adverse events.

**Table 2 pcn570064-tbl-0002:** The SPIRIT schedule of these psychometric assessments.

	At baseline	Days 5–6	Week 2	Week 4	Week 6	When dropping out
MADRS	✔	✔	✔	✔	✔	✔
CGI‐S	✔	✔	✔	✔	✔	✔
CGI‐I		✔	✔	✔	✔	✔

Abbreviations: CGI‐I, Clinical Global Impression‐Improvement Scale; CGI‐S, Clinical Global Impression‐Severity Scale; MADRS, Montgomery Åsberg Depression Rating Scale.

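### Last-observation-carried-forward fills missing Week 2–6 scores by assuming no change after a five-day treatment; this can bias the secondary comparisons in either direction but leaves the any-week primary outcome intact

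*Protocol article*

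**What the plan says.** All references are to the protocol article.

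- **Statistical analysis, missing data:** "The data will be analyzed on a full analysis set, with endpoint analysis using the" LOCF method. No outcome is named or exempted.
- **Statistical analysis, population:** "The full analysis set will include all patients who agree to provide a baseline and at least one postbaseline data measurement".
- **Statistical analysis, tests:** "Response and remission rates will be evaluated using a" chi-square test. For the continuous score, "In Week 6, the MADRS score will be calculated using generalized linear mixed models". Whether the model takes observed or LOCF-filled scores is not stated.
- **Primary and secondary outcome measures:** "The response rate at any given week of" follow-up is the primary outcome. Response, remission, MADRS change and CGI scores at the first post-baseline visit and at Weeks 2, 4 and 6 are secondary. Table 2 also schedules MADRS, CGI-S and CGI-I when a participant drops out.
- **Intervention:** "Ten sessions will be applied per day (18,000 pulses/day) for 5 consecutive days (90,000 pulses in total"). The first post-baseline visit therefore falls at or just after the end of stimulation.

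**The concern.** Every visit after the first measures whether the effect of a five-day course lasts, grows or fades. LOCF answers that question by assumption for anyone who leaves: the last score seen stands in for Week 6. If the effect fades in that participant, the carried score is too favourable; if it was still developing, the carried score is too unfavourable.

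The plan also puts two ways of handling missing MADRS scores side by side without reconciling them. A mixed model fitted to the observed repeated scores uses incomplete participants directly under missing at random and needs no filling-in. The same model fitted to LOCF-filled scores would treat carried values as measured ones.

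At stake are the secondary Week 2, 4 and 6 comparisons, which are the trial's evidence on durability.

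**Working it through.** **1. The plan's own figure.** Inputs from Sample size calculation: 85.7% and 26.7% response, two-sided 0.05, 80% power, chi-square test, about 7% dropout.

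n per arm = [1.960·√(2·p̄·(1−p̄)) + 0.842·√(p₁(1−p₁) + p₂(1−p₂))]² / (p₁−p₂)², with p̄ = (0.857 + 0.267)/2 = 0.562.

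- First term: 1.960 × √0.4923 = 1.375.
- Second term: 0.842 × √(0.1226 + 0.1957) = 0.475.
- n = (1.850)² / (0.590)² = 3.42 / 0.348 = 9.8, so 10 per arm.
- Dropout: 10 / 0.93 = 10.8, so 11 per arm.

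The stated 11 per arm is reproduced. Power by the normal approximation is 80.8% at 10 and 84.9% at 11 per arm. Handling missing data differently at Week 6 does not change this number.

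**2. How many participants are exposed.** 22 × 0.07 = 1.54 expected dropouts over both arms, fewer than one per arm on average.

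**3. Visit-specific rates.** With 11 analysed in an arm, one participant who had responded when last seen and whose status is carried to Week 6 contributes 1/11 = 9.1 percentage points to that arm's Week 6 response rate.

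**4. Any-week response.** A participant is a responder if any observed post-baseline score shows at least a 50% reduction. LOCF appends copies of the last observed score, so it can neither add a first response nor remove an earlier one. A simulation with random response patterns and random last visits agrees: 0 of 50,000 participants changed status.

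**5. Week 6 mean MADRS difference.** Let d be the share of an arm whose score is carried, and r the rebound (true Week 6 score minus carried score) in those participants. Then

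bias in favour of aiTBS = d(aiTBS)·r(aiTBS) − d(sham)·r(sham).

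The documents give no value for r; 5 to 10 points is an assumption used to show the range.

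| Share carried, aiTBS / sham | Rebound, aiTBS / sham | Bias in MADRS points (positive favours aiTBS) |
|---|---|---|
| 7% / 7% | equal | 0 |
| 7% / 7% | 5–10 / 0 | +0.35 to +0.70 |
| 1 of 11 / none | 5–10 / any | +0.45 to +0.91 |
| none / 1 of 11 | any / 5–10 | −0.45 to −0.91 |
| 2 of 11 / none | 5–10 / any | +0.91 to +1.82 |

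For example, 1/11 × 10 = 0.91 and 2/11 × 10 = 1.82. If the missing score would have improved instead, r is negative and the sign reverses.

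**The case against.** The case for leaving the text alone has real force.

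- **The dropout visit.** Table 2 schedules a MADRS when a participant drops out, so for many the carried score will be later than the end of stimulation. This stands, and it weakens the worry. It does not remove it, because that score is still carried unchanged to Week 6.
- **Few dropouts, no fixed sign.** A reader might infer that Week 6 effects will be biased, or biased towards aiTBS. The documents do not support that. The bias is zero with equal dropout and equal rebound, and otherwise takes either sign.
- **The primary outcome.** A reader might infer from the endpoint-analysis wording that the primary result could be computed two ways, with a participant who responds at Week 2 and relapses by Week 6 counted differently. But the outcome section fixes the primary as response at any week, the sample size is built on that quantity, and Week 6 response is listed separately as secondary. A missing-data method does not redefine a stated endpoint. What remains is loose wording that one sentence would settle.
- **Redundancy.** A reader might call LOCF redundant next to the mixed model. That can apply only to the MADRS score. Response and remission go to a chi-square test and need some rule for missing values.
- **Model input and precision.** The article never says that the model is fitted to filled data, and an article may leave model detail to a fuller document. So it cannot be claimed that the model will treat carried values as observed, or that standard errors will be too small. The unrestricted LOCF instruction, however, is stated text and not an omission.

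**Conclusion.** The point holds for the secondary outcomes. LOCF without limit to particular outcomes suits this design poorly because it assumes, for early leavers, the durability that Weeks 2 to 6 are meant to test, and the plan already contains a better tool for MADRS.

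Over the cases worked, the Week 6 mean difference shifts by −0.9 to +1.8 MADRS points, and one carried responder is worth 9.1 percentage points in an arm. These sizes rest on the assumed 5–10 point rebound, on up to two carried participants in one arm, and on 11 analysed per arm.

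The primary outcome and the planned 11 per arm are untouched. This is worth correcting before unblinding, but it does not put the primary test in doubt.

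**What to change.** 1. **MADRS:** fit the mixed model to observed scores at all four post-baseline visits, with arm, visit, arm-by-visit and baseline MADRS, and read the Week 6 contrast from it. Use no LOCF-filled values. Say how a dropout assessment is assigned to a visit.
2. **Primary:** state that it is response at any post-baseline assessment, as the outcome section defines it, and not a last-value endpoint. Count a participant with no observed response as a non-responder, and say whether the dropout assessment counts. Among participants in the full analysis set who are assessed at scheduled visits, this gives the same classification as the present definition.
3. **Visit-specific response and remission:** count missing as non-response, and report LOCF only as a labelled sensitivity analysis.

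The cost is analysis wording before unblinding, with no new data or participants. There are trade-offs. Counting missing as non-response is itself a conservative single imputation: a true Week 6 responder who left would lower that arm's rate by the same 9.1 points. The mixed model relies on missing at random. Showing LOCF alongside lets a reader see whether the choice matters.

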### Ethics and dissemination

This research protocol was peer‐reviewed and approved by the Ethical Review Board of Fujita Health University (CR24‐028). This research will be conducted in accordance with the Declaration of Helsinki and the Ethical Guidelines for Medical and Biological Research Involving Human Subjects as certified by the Japanese Ministry of Education, Culture, Sports, Science and Technology; the Ministry of Health, Labour, and Welfare; and the Ministry of Economy, Trade and Industry. Any protocol amendments (changes to eligibility criteria, outcomes, and analyses) that are necessary will be communicated and modified in the relevant parties. All required documents, including the study protocol, informed consent form, participant information leaflet, and any other documents have been reviewed and approved by the Ethics Review Committee of Fujita Health University on August 14, 2024.

Following screening, we will invite potentially eligible patients to join our study. All procedures involved, including the potential benefits and risks, will be discussed in detail. They will also be informed that participation in the study is entirely voluntary, and their treatment will not be affected if they decline to participate. All questions and concerns will be addressed in detail. Participants who satisfy the inclusion but not the exclusion criteria can only be recruited after providing written informed consent. Every participant's personal information will be strictly confidential. Serial numbers will be used instead of real names when analyzing data.

We acknowledge funding from the Japan Agency for Medical Research and Development (24dk0307129h0001). The funding source will play no role in the study's design and execution, data collection, management, analysis, interpretation, manuscript preparation, review, approval, or decision to submit the manuscript for publication. For each visit, participants in this study will receive a monetary compensation of 10,000 Japanese yen. The study data will be collected and managed using REDCap electronic data capture tools hosted at Fujita Health University School of Medicine.^37^, ^38^ REDCap is a secure, web‐based software platform designed to support data capture for research studies. It includes (1) an intuitive interface for validated data capture; (2) audit trails for tracking data manipulation and export procedures; (3) automated export procedures for seamless data downloads to common statistical packages; and (4) data integration and interoperability procedures with external sources. Access to study data in REDCap will be restricted to study team members who have authenticated using Fujita Health University credentials.

Data is handled, computerized, and stored in accordance with the Clinical Trials Act of 2017. Paper copies of trial‐related documentation are annotated, signed, and dated before being filed in the electronic medical records. The Principal Investigator is responsible for the overall quality and retention of trial data. All trial data are retained following the most recent Directive on GCP (2005/28/EC) and local policy.

Staff collect clinical and safety data for trial participants, which are then recorded in the electronic case report form (eCRF) of the clinical data management system REDCap and password‐protected trial spreadsheets. The eCRFs and trial spreadsheets utilize unique trial identifier numbers to identify participants. A Data Monitoring Committee evaluates patient safety in a clinical trial of an investigational intervention through periodic review of adverse events and clinical safety assessments. Posttrial care of the study participants is ensured by the possibility of further treatment in the standard care setting.

Study results will be disseminated through publication in international peer‐reviewed journals and conference presentations to mental health professionals.

## DISCUSSION

A recent network meta‐analysis elucidated that olanzapine plus fluoxetine, quetiapine, olanzapine, lurasidone, lumateperone, cariprazine, and lamotrigine were more effective than placebo at reducing depressive symptoms,^7^ although 30%–50% of individuals with BDep are refractory to pharmacological treatments.^8^, ^9^, ^10^, ^11^ Thus, we believe that developing a novel treatment for these people is warranted. The proposed study will be the first to use an RCT to explore the effects of a high‐dose iTBS (L‐DLPFC) protocol on TR‐BDep. We anticipate that people receiving our aiTBS (L‐DLPFC) treatment will experience significant improvements in depressive symptoms compared to those receiving sham treatment. According to the SNT study, the aiTBS (L‐DLPFC) protocol was well tolerated by the participants.^24^ This study will provide important evidence for TR‐BDep patients and clinicians.

Our study protocol has several limitations. First, the period during which response to the drug is evaluated may be short (minimum 2 weeks). Second, our study allows the use of concomitant medications. Because benzodiazepine administration may inhibit rTMS response, whereas psychostimulant use may be associated with a greater rTMS response,^39^, ^40^ the medications might influence the study results. Third, the SNT study is often stimulated at approximately 110% of the RMT after correction.^23^, ^24^ Because the protocol in our study does not use individual navigation for each participant, depth correction might be difficult to implement, raising concerns that the stimulation intensity may be low. Fourth, the range of interval session in our study is 30–50 min, and the factor might be a confounding factor. We will report an association between factors that will be included in the statistical analysis as a variable and the results of our study in the next paper.

## ETHICS APPROVAL STATEMENT

The protocol for this research project has been approved by a suitably constituted Ethics Committee of the institution and it conforms to the provisions of the Declaration of Helsinki. Committee of Fujita Health University, Approval No. CR24‐028.

## PATIENT CONSENT STATEMENT

Following screening, we will invite potentially eligible patients to join our study. All procedures involved, as well as the potential benefits and risks, will be discussed in detail. They will also be informed that participation in the study is entirely voluntary, and their treatment will not be affected if they decline to participate. All questions and concerns will be addressed in detail. Participants who meet the inclusion but not the exclusion criteria can only be recruited after providing written informed consent. Every participant's personal information will be kept strictly confidential. Serial numbers will be used instead of real names when analyzing data.

## CLINICAL TRIAL REGISTRATION

The study has been registered with Japan Registry for Clinical Trials under the identifier jRCTs042240019.

## Data Availability

As our research dataset contains potentially sensitive information, we have ethical restrictions. Please contact the Institutional Review Board of the Ethics Committee when requesting data.
